### Collaborators and setting

The FAIR study is being conducted by the National Institute for Medical Research (NIMR) in Tanzania, the University of Oxford, CWBSA, and Pact Tanzania. The study will be conducted in eight districts of rural and semi-urban Tanzania: Kyela District Council (DC), Mbeya DC, Muleba DC, Shinyanga DC, Shinyanga Municipal Council, Kahama Town Council, Msalala DC, and Ushetu DC. PLH-Teens will be delivered by teachers in schools and in communities by volunteers (compensated with an honorarium) (*N* = 444) with Furaha program coaches (*N* = 70) providing facilitators with ongoing supervision. Facilitators will deliver the program via the coordination of five LIPs—Humuliza, Tadepa, Integrated Rural Development Organisation, Caritas, and Tanzania Red Cross Society.

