### Secondary quantitative data collection

The study will analyze the following anonymized secondary process and outcome data from Pact Tanzania and CWBSA: pre-post surveys completed by parent/caregivers (*N* = 50,000); pre-post surveys completed by adolescents (*N* = 50,000); parent/caregiver and adolescent program attendance registers (*N* = 100,000 participants); facilitator demographic questionnaires (*N* = 444); coach demographic questionnaires (*N* = 70); coach assessments of facilitators (*N* = 444); CWBSA assessments of coaches (*N* = 70); LIP organizational surveys (*N* = 5); and implementation cost surveys (*N* = 300).

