#### Quantitative analyses

Quantitative data will be cleaned using Stata and analyzed in Stata and R using methods such as correlation and regression analyses, as well as structural equation models. The frequencies and distribution of each variable will be examined to check for any implausible values as well as to select the appropriate analysis method (e.g., a suitable regression link function). When there are more than two items in a given scale, coefficients such as Cronbach Alphas or Omegas will be used to assess the item-level reliability of the measures. Where possible, mixed effect models will be utilized to account for nesting within parenting groups [53]. Missing data will be addressed appropriately by considering the complete case observations as well as using full information maximum likelihood or multiple imputation, as appropriate [54, 55]. Where relevant, TREND guidelines will be used when reporting quantitative results [56].

#### Research question 1

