The level of implementation of PLH-Teens delivery will be determined by analyzing data from family attendance registers; facilitator assessments; coach assessments; structured observations of group sessions; interviews held with facilitators, coaches, and LIP staff; and FGDs held with adolescents, parents/caregivers, facilitators, and coaches. Attendance rates and attendance trends among parents/caregivers and adolescents, as well as variations in attendance, and program completion rates will be calculated based on the attendance registers to determine the extent of participation in PLH-Teens. The level of competent adherence with which facilitators deliver the program will be determined using the results from the Facilitator Assessment Tool assessments completed by coaches. To examine the reliability and validity of the Facilitator Assessment Tool, a psychometric evaluation consisting of content validity (stakeholder perspectives from interviews and focus groups with facilitators, coaches, and CWBSA staff), intra-rater reliability (percentage agreements and intra-class correlations), inter-rater reliability (percentage agreements and intra-class correlations), internal consistency (Cronbach Alphas), construct validity (exploratory factor analyses), and predictive validity analyses will be performed. Similarly, the level of competent adherence with which coaches deliver facilitator supervision will be determined using the results from the Coach Assessment Tool assessments completed by CWBSA staff. Interviews, FGDs, and session observations will be used to expand upon and contextualize the findings regarding the demographic, attendance, facilitator competent adherence, and coach competent adherence data.

#### Research question 2

Factors associated with the quality of implementation will be examined using the socio-demographic data from the Facilitator and Coach Profile Forms; LIP organizational characteristics surveys; interviews; FGDs; and structured observations of group sessions. Correlation and regression analyses will be used to examine the relationship between facilitator and coach competent adherence and their associations with family, facilitator, coach, and organizational characteristics. Interviews, FGDs, and session observations will be used to expand upon and contextualize the findings.

#### Research question 3

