A variety of data sources will be used to examine how implementation is associated with changes in VAC and family well-being. In particular, correlation and regression analyses will be used to look at whether pre-post changes in family outcomes are associated with family attendance, facilitator and coach competent adherence, and facilitator and coach characteristics, as well as LIP characteristics. Interviews, FGDs, and session observations will be used to expand upon and contextualize the findings.

#### Research question 4

Participant and implementing staff perspectives on the acceptability, appropriateness, feasibility, benefits, and challenges of delivering PLH-Teens in their communities will be examined by analyzing the interviews, FGDs, and session observations with school principals, facilitators, coaches, LIP staff, CWBSA staff, adolescents, and parents/caregivers.

#### Research question 5

Changes in VAC and participant well-being will be analyzed based on data gathered from parent/caregiver pre-post questionnaires, adolescent pre-post questionnaires, interviews, and FGDs. Multi-level models will be used to examine differences in pre- to post-intervention family-level outcomes and to compare differences in outcomes reported by both adolescents and parents/caregivers. Variation in the pre-post changes will be examined by participant baseline characteristics, and, if possible, by parenting group and LIP. The analyses will be similar to treatment-on-the-treated analyses since all participants included in the monitoring data would have engaged with the program to some extent. The levels of change reported by participants will be compared to the levels of change reported by the treatment and control groups in the randomized trial of the program in South Africa. Where possible, the reliability of the family survey items will also be examined using coefficients such as Cronbach Alphas or Omegas.

The findings from the interviews and FGDs  will also be analyzed to explore participant perspectives on the impacts of the program on them and their families. The interviews and FGDs will also reveal what impact implementing volunteers and staff assess the program had and will have on themselves, participants, schools, and communities.

#### Research question 6

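### Research questions 2 and 3 plan regressions on LIP characteristics, but there are only five LIPs and the only nesting committed to is the parenting group, so these tests cannot hold their nominal error rate if LIPs differ

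*Protocol article*

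**What the plan says.** The number of LIPs is fixed. Under Collaborators and setting, "Facilitators will deliver the program via the coordination of five LIPs". Secondary quantitative data collection lists the "LIP organizational surveys" with N = 5, so there is one row of organizational data per LIP.

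Two research questions use those rows as predictors:

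- **Research question 2** applies correlation and regression analyses to facilitator and coach competent adherence and "their associations with family, facilitator, coach, and organizational characteristics".
- **Research question 3** applies them to pre-post changes in family outcomes, with predictors that include family attendance and the adherence and characteristics of facilitators and coaches, "as well as LIP characteristics".

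Table 4 names the LIP Organizational Characteristics Form as a data source for both.

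On clustering, the general paragraph under Quantitative analyses says: "Where possible, mixed effect models will be utilized to account for nesting within parenting groups". LIP appears as a level in one other place, under research question 5: "Variation in the pre-post changes will be examined by participant baseline characteristics, and, if possible, by parenting group and LIP". Nothing in the article limits LIP characteristics to description or remarks that there are only five LIPs.

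**The concern.** A characteristic of an LIP is constant within that LIP, so it takes at most five values however many families or facilitators contribute data. The relevant sample size for its coefficient is five.

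A model with a random intercept for parenting group only does not reflect this. Variation between LIPs is absorbed into the group intercept, and the groups are then treated as independent information about a predictor that varies only between LIPs. In question 2 the outcome belongs to the facilitator, so with no LIP term the facilitators play that part. Either way, the standard error of the LIP coefficient is too small whenever LIPs differ for reasons other than the characteristic tested.

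Staff and organizational factors are an announced contribution of the study (Background), and its results are meant to inform how delivery is modified in Tanzania and elsewhere (Conclusion). Table 3 indicates that LIPs applied to work in specific districts, so a contrast between LIPs is also partly a contrast between places. A chance or geographic difference among five partners could be read as an organizational factor.

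**Working it through.** The article states no alpha, power or ICC for these analyses, so there is no figure of the plan's own to reproduce.

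**Inputs from the article.** There are 5 LIPs, about 50,000 dyads (10,000 per LIP if balanced) and 444 facilitators (444/5 = 88.8, about 89 per LIP).

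**Assumptions.**
- Two-sided alpha is 0.05, the layout is balanced, total variance is 1 and the group ICC is 0.05.
- The LIP ICC is 0, or runs from 0.002 to 0.02.
- Group size in the main case is taken from Session observations: 150 participants / 5 sessions = 30, or 15 dyads. The caregiver numbers agree: 155 in total less 80 in focus groups leaves 75, and 75/5 = 15. This gives 50,000/15 = 3,333 groups, about 667 per LIP.
- A deliberately low alternative uses 44 groups of 225 dyads per LIP (44 × 225 = 9,900).

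**Step 1: what five units allow.** With one predictor, residual df = 5 − 2 = 3 and the critical t is 3.182. The critical correlation is t/√(t² + 3) = 3.182/√(10.128 + 3) = 0.878. Two predictors leave 2 df, three leave 1 and four leave none.

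**Step 2: question 3 with a group intercept only.** Let L be the LIP ICC, g the group ICC, m the groups per LIP and n the dyads per group.

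- True variance of an LIP mean: L + g/m + (1 − L − g)/(mn)
- Variance the model uses: (L + g)/m + (1 − L − g)/(mn)
- Type I error: 2 × [1 − Φ(1.96/√(true/model))]

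Example with L = 0.002, m = 667, n = 15:
- true = 0.002 + 0.000075 + 0.000095 = 0.002170
- model = 0.000078 + 0.000095 = 0.000173
- ratio = 12.56, whose root is 3.54
- type I error = 2 × [1 − Φ(0.553)] = 58%

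Example with L = 0.002, m = 44, n = 225:
- true = 0.002 + 0.001136 + 0.000096 = 0.003232
- model = 0.001182 + 0.000096 = 0.001278
- ratio = 2.53, whose root is 1.59
- type I error = 22%

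**Step 3: question 2 with facilitator adherence, one assessment each and no LIP term.** True variance is L + (1 − L)/89 and the model uses 1/89. At L = 0.002, 0.013213/0.011236 = 1.176, whose root is 1.08, and type I error is 7%.

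| LIP ICC | Q3, 667 groups per LIP | Q3, 44 groups per LIP | Q2, 89 facilitators per LIP |
|---|---|---|---|
| 0 | 5% | 5% | 5% |
| 0.002 | 58% | 22% | 7% |
| 0.005 | 72% | 36% | 10% |
| 0.01 | 79% | 48% | 15% |
| 0.02 | 85% | 58% | 24% |

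Across ICCs 0.002 to 0.02, the standard error is too small by a factor of about 3.5 to 10.1 in the second column, 1.6 to 3.5 in the third and 1.1 to 1.7 in the fourth. Coach adherence, the other question 2 outcome, has 70/5 = 14 coaches per LIP, so its inflation at the same ICC would be smaller still.

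**Step 4: simulation check.** There were 4,000 data sets per setting, with a binary LIP factor split 2 versus 3 and no true effect. At ICCs 0.005, 0.01 and 0.02, rejection rates were 71%, 79% and 85% with 667 groups per LIP, and 39%, 50% and 61% with 44. Regression on the five LIP means with 3 df rejected in 4.7% to 5.3% of runs.

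**The case against.** Several counter-arguments deserve an answer.

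**Model detail belongs in the analysis plan.** The article speaks of example methods, states no alpha or LIP-level hypothesis, and leaves random-effect levels open. That is fair for the choice of error term. But regression on LIP characteristics is positively stated, and no later document can supply more than five LIPs. An LIP random intercept would have its variance estimated from five units, and LIP fixed effects would make LIP characteristics inestimable.

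**LIP is a recognised level.** Research question 5 commits to multi-level models and mentions LIP. A reader might infer that the plan ignores LIP altogether, which the text does not support. The mention is nevertheless conditional, concerns variation in change, and gives questions 2 and 3 no LIP-level error term.

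**The damage is conditional.** A reader might infer that any LIP factor will come out significant. It will not: the rate is 5% if LIPs do not differ, and otherwise depends on ICCs and group numbers that the article does not give. A reader might also infer that standard errors are several times too small in both questions. In question 2 the factor is only about 1.1 to 1.7 over the ICCs considered. Nor would 50,000 families count as independent under a group-intercept model, where the nominal information is the groups.

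**The findings are framed cautiously.** Questions 2 and 3 speak of associations set beside qualitative data, and the Discussion acknowledges flawed and sparse data and promises sensitivity checks. The article does not say that LIP associations will be presented as drivers. This tempers the consequence but does not make the test valid.

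**Conclusion.** The point stands in limited form. Questions 2 and 3 plan regressions on a predictor with five independent units, and the stated nesting does not protect its test. Useful inference on LIP characteristics is not available: a test at the right level keeps its 5% error rate but needs |r| of at least 0.878. A test following the stated nesting exceeds 5% whenever LIPs differ, severely in question 3 if groups are many and modestly in question 2. The sizes rest on assumed ICCs, an assumed number of groups and a balanced layout. The count of five and the 3 degrees of freedom rest on none of these. The point does not extend to facilitator adherence or attendance as predictors, which are the core of question 3 and are measured on far more units.

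**What to change.** In research questions 2 and 3, remove LIP and organizational characteristics from the tested regression predictors. Report differences between the five LIPs descriptively, alongside the organizational survey and the qualitative data, and state that LIP-level associations are not tested because n = 5.

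Adjusting facilitator- and family-level models for LIP with four indicators is a reasonable option but is not needed to meet this point. Its downside, which should be stated if it is used, is that the other coefficients become within-LIP estimates.

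The change is one of wording and needs no new data. What is lost is a set of p-values for LIP characteristics that five units cannot usefully support.

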## Methods

This mixed-methods study involves the integration of quantitative and qualitative methods to address the research questions. The data sources to be used are outlined in Table 1. Qualitative (including focus group discussions, in-depth interviews, and observation) and quantitative (merged secondary data collected via routine monitoring and evaluation by Pact Tanzania, local implementing partners or LIPs, and Clowns Without Borders South Africa or CWBSA) methods will be used to explore the impact, acceptability, appropriateness, feasibility, fidelity, and cost of PLH-Teens. As randomization to intervention and control groups is not possible, the study will make the most of the routine service delivery data available. Analyzing this data will allow for a unique inquiry into the real-world implementation of a parenting program at scale.

**Table 1 Tab1:** Matrix of data collection methods

Type of data	Data collectors	Data collection method	Study participants
Primary data	FAIR research team	Focus group discussions	Adolescents
			Parents/caregivers
			Furaha facilitators and coaches
		In-depth interviews	Program coordinators and directors
			Pact Monitoring and Evaluation (M&E) team
			Furaha facilitators and coaches
			School principals
		Structured observations	Furaha Teens group sessions
			Furaha Teens coaching sessions
		Community of practice meeting	LIP and Pact staff
		Document review	All of the above
Secondary data	Pact Tanzania and LIPs (collected by Furaha facilitators) and other team members	Family reports of parenting practices, child behavior, child and caregiver mental health (routine data)	Parents/caregivers and adolescents
		Family enrolment, attendance, engagement, and dropout	
		Cost data	Facilitators, coaches, and LIP staff
		Surveys on the sociodemographic and professional background of facilitators and coaches delivering the program	Furaha facilitators and coaches
	CWBSA	Assessments of facilitator competent adherence	Furaha facilitators and coaches
		Assessments of coach delivery of facilitator supervision sessions	

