### Study participants

The study will collect primary data from 48 program coaches, 96 program facilitators, 58 Pact Tanzania and LIP staff, eight school principals, three CWBSA staff, 155 parents/caregivers, and 155 adolescents. The study will also collect anonymized secondary data from approximately 50,000 parent-child dyads (*N* = 100,000), 444 program facilitators, 70 program coaches, and five LIPs. The inclusion criteria used to select study participants for primary and secondary data collection are outlined in Tables 2 and 3.

**Table 2 Tab2:** Inclusion criteria for primary data study participants

Study participant group	Primary data inclusion criteria
Program Coaches (*N* = 70)	• Attended the Furaha Teens coach training workshop; and • Provided coaching to facilitators during the implementation of Furaha Teens.
Program Facilitators (*N* = 444)	• Teachers or community volunteers; • Attended the Furaha Teens facilitator training workshop; and • Implemented the Furaha Teens program.
Pact Tanzania and LIP Staff (*N* = 58)	• Staff member working for either Pact Tanzania or one of the LIPs delivering Furaha Teens.
School Principals (*N* = 8)	• Principal in a school where Furaha Teens was delivered.
CWBSA Staff (*N* = 3)	• Staff member working for CWBSA involved in the implementation or research associated with the FAIR Study.
Parents/caregivers (*N =* 155)	• Aged 18 or older; • Primary caregiver responsible for the care of an adolescent between the ages of 9 and 14 who attended the Furaha Teens program; and • Attended in the Furaha Teens program.
Adolescents (*N =* 155)	• Aged 9 to 14; • Consent provided by primary caregiver responsible for the adolescent’s well-being; • Assent provided by the adolescent; • Primary caregiver responsible for their care attended the Furaha Teens program; and • Attended in the Furaha Teens program.

**Table 3 Tab3:** Inclusion for secondary data study participants

Study participant group	Secondary data inclusion criteria
Adolescents (*N =* 50,000)	• Adolescent girl aged 9 to 14; • Participated in the Kizazi Kipya Project; • In the same household as her parent/caregiver at least 4 days a week; • Parent/caregiver attended the Kizazi Kipya Project; • Consent provided by primary caregiver responsible for the adolescent’s well-being; and • Assent provided by the adolescent.

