Parents/caregivers (*N =* 50,000)	• Aged 18 or older; • Primary caregiver responsible for the well-being and care of an adolescent girl between the ages of 9 and 14 who participated in the Kizazi Kipya Project; and • Attended the Kizazi Kipya Project.
Program Facilitators (*N* = 444)	• Attended a Furaha Teens facilitator training workshop; and • Facilitated Furaha Teens sessions.
Program Coaches (*N* = 70)	• Attended a Furaha Teens coach training workshop; and • Provided coaching to facilitators during the implementation of Furaha Teens.
LIPs (*N* = 5)	• Submitted a Request for Application (RFA) to the Kizazi Kipya Project to implement Furaha Teens in specific districts; and • Selected by Pact Tanzania to implement Furaha Teens.

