RQ4: What are participant and implementing staff perspectives on the acceptability, appropriateness, feasibility, benefits, and challenges of delivering PLH-Teens in their schools and communities?	1) Interviews with school principals, facilitators, coordinators, coaches, and LIP staff 2) FGDs with adolescents, parents/caregivers, facilitators, and coaches 3) Direct observation of group sessions using the structured observation guide
RQ5: What is the impact of PLH-Teens on VAC and participant well-being?	1) Parent/caregiver- and adolescent-report on pre-post questionnaires 2) Individual interviews with school principals, facilitators, coordinators, coaches, and LIP staff 3) FGDs with adolescents, parents/caregivers, facilitators, and coaches
RQ6: How much does it cost to deliver PLH-Teens at scale?	1) Facilitator cost surveys 2) Facilitator profile surveys 3) Coach cost surveys 4) LIP cost surveys

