### Data quality and potential biases

Collecting comprehensive assessments of family-level outcomes from 100,000 beneficiaries is challenging. As a result, the study relies on existing data collection tools and processes developed and used during program implementation by Pact Tanzania’s Monitoring and Evaluation team. If timing allows, the research team will conduct random checks to verify the quality of implementation and outcome data. Among the observational facilitator and coach assessments, CWBSA will double code a random sample of program delivery videos to verify the accuracy and reliability of the assessments. As a significant amount of study data relies on self-reports, this data could be limited by recall and social desirability bias.

Where relevant, the study will take into consideration advice regarding how to manage and analyze data with FUPS characteristics (flawed, uncertain, proximate, and sparse), such as by presenting the data flow, conducting statistical sensitivity checks, and making the analyses accessible [57]. In the event of missing outcome data on individuals who are eligible but not included in the sample, sensitivity analysis will be done by replacing missing data with simulated data.

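### RQ5 is labelled similar to treatment-on-the-treated, but with one group and no concurrent control it estimates uncontrolled pre-post change among participants

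*Protocol article*

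**What the plan says.** All references are to the protocol article.

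- **Question.** Table 4 words RQ5 causally: "What is the impact of PLH-Teens on VAC and participant well-being".
- **Design.** The opening of Methods states: "As randomization to intervention and control groups is not possible, the study will make the most of the routine service delivery data available". No concurrent comparison group is described anywhere.
- **Model.** Under Research question 5: "Multi-level models will be used to examine differences in pre- to post-intervention family-level outcomes".
- **Label.** The same paragraph adds: "The analyses will be similar to treatment-on-the-treated analyses since all participants included in the monitoring data would have engaged" with the program at least partly. The next sentence plans to set the observed change beside the change in both arms of the South African trial.
- **Who is in the data.** Table 3 admits adolescents who "Participated in the Kizazi Kipya Project" and caregivers who "Attended the Kizazi Kipya Project". The section PLH-Teens in Tanzania describes Kizazi Kipya as the broader project for orphans and vulnerable children within which Furaha Teens is delivered. Table 2, for the primary data, uses attendance at Furaha Teens itself.
- **Missing data.** Quantitative analyses plans complete-case results together with full information maximum likelihood (FIML) or multiple imputation. Data quality and potential biases adds that "sensitivity analysis will be done by replacing missing data with simulated data", for people who met the criteria but are absent from the sample.

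**The concern.** A treatment-on-the-treated effect compares treated people with their own untreated outcome. The plan justifies the label only by saying that everyone analysed took some part. That fixes the population and leaves the untreated outcome unknown. What the model returns is the change from before to after in one group.

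That change can contain much besides the program: secular change (the protocol records COVID-19 disruption), maturation of girls aged 9 to 14, regression to the mean, and reporting bias. Data quality and potential biases names recall and social desirability only. Table 1 shows that the family reports are collected by Furaha facilitators and other team members, so changed reporting after the course is a live possibility.

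At stake is what RQ5 may conclude. The Research uptake strategy and the Conclusion send the findings into guidelines, policy briefs and delivery advice for Tanzania and 24 other countries. A label borrowed from trial analysis invites readers to take the change as a causal effect in the treated.

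**Working it through.** The plan gives no effect size, standard deviation, dropout rate or sample-size calculation for RQ5, so there is no figure to reproduce. Every value in SD units below is an assumption, with positive meaning improvement.

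**1. What the model estimates.** Let B be the baseline outcome, Y1 the post outcome with the program and Y0 the post outcome the same family would have had without it.

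- Treatment-on-the-treated effect: τ = E[Y1 − Y0 | engaged].
- RQ5 model: E[Y1 − B | engaged] = E[Y1 − Y0 | engaged] + E[Y0 − B | engaged] = τ + s.

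Both lines condition on engagement, so universal engagement does not remove s. The two agree only if s = 0, and one group cannot show that.

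| Program effect τ | Background change s | Observed τ + s |
|---|---|---|
| 0 | 0.2 | 0.20 |
| 0.2 | 0.1 | 0.30 |
| 0.3 | −0.1 | 0.20 |
| 0.3 | 0 | 0.30 |

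Rows 1 and 3 give the same result from opposite truths, so the error can go either way.

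**2. Size does not help.** Take 50,000 dyads, a change SD of 1, cluster sizes of 20 to 113 (50,000 / 444 facilitators = 112.6) and intraclass correlations (ICC) of 0.01 to 0.10. The 95% half-width is 1.96 × √[(1 + (m − 1) × ICC) / 50,000].

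- m = 20, ICC 0.01: 1.96 × √(1.19 / 50,000) = 0.0096.
- m = 113, ICC 0.10: 1.96 × √(12.2 / 50,000) = 0.0306.

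A background change of 0.1 SD would be 3 to 10 half-widths (0.1 / 0.0306 = 3.3; 0.1 / 0.0096 = 10.4). It would look conclusive with no program effect at all.

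**3. The South African arms.** They come from another country and another time. Background reports that trial's effects at 5 to 9 months' follow-up. Tanzania delivers a locally adapted, HIV-enhanced version (PLH-Teens in Tanzania) and measures with shortened tools (Family outcome and demographic measures). The South African control arm therefore does not estimate s for Tanzanian families.

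**4. The analysis set.** RQ5 presumes engagement with the program. Table 3 requires participation in, or attendance at, the host project. A family can satisfy Table 3 without that establishing engagement with Furaha Teens, so the premise needs a Furaha Teens criterion that Table 3 does not contain.

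**5. Families without a post survey.** If a share d lacks post data, the bias of the mean change among those retained, relative to all who started, is d × (change in retained − change in lost). With 0.3 in those retained:

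| Change in those lost | d = 10% | d = 30% | d = 50% |
|---|---|---|---|
| 0 | +0.03 | +0.09 | +0.15 |
| 0.2 | +0.01 | +0.03 | +0.05 |
| 0.3 | 0 | 0 | 0 |
| 0.4 | −0.01 | −0.03 | −0.05 |

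The sign depends on an outcome that the documents do not give.

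**The case against.** The strongest defence is that the protocol hides nothing. It says randomization is not possible, the RQ5 text speaks of changes, the label is hedged as a similarity, TREND reporting is adopted, and the result is to be set beside a randomized trial. Engagement arguably follows from the data source, since facilitators collect much of the monitoring data, and the wording covers partial attenders.

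Much of this stands. It makes the Table 3 mismatch an inconsistency to tidy, not proof that the engagement premise is false. It also means that calling the analysis completers-only would be inaccurate. It does not rescue the label, because neither openness about the design nor an external benchmark supplies the untreated outcome.

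A reader might also infer that the Kizazi Kipya criterion removes families who drop out. The documents do not support that. Table 3 sets no Furaha Teens session minimum or completion rule, and Study recruitment and informed consent places the research invitation at enrolment in the host project. A family that leaves Furaha Teens early still qualifies, and Table 1 lists dropout among the recorded data.

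**Conclusion.** The treatment-on-the-treated description is wrong as written. RQ5 estimates uncontrolled pre-post change among participants and identifies no treatment effect. This follows from the design and needs no numerical assumption. Its size cannot be derived from the documents; the figures above only illustrate that the error may run in either direction. The Table 3 wording is a secondary inconsistency.

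Four stronger readings should be resisted:

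- **That change is overstated.** It may be, if early leavers lack post surveys and improve less. No dropout rate or outcome for leavers is given, and FIML or multiple imputation is already planned.
- **That completion rates are inflated.** Research question 1 computes them from attendance registers, enrolment is recorded, and no attended-only denominator is specified.
- **That full retention is assumed.** The 50,000 beside "pre-post surveys completed by parent/caregivers" matches the approximate reach. It is a planning figure, and the missing-data plan presupposes incomplete pairs.
- **That simulated values will be treated as observed.** The simulation is an added sensitivity analysis, and nothing says it is a single fill-in.

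**What to change.** 1. Under Research question 5, delete the treatment-on-the-treated sentence. State instead that RQ5 estimates uncontrolled pre-post change among participants, that no treatment effect is identified, and that secular change (including COVID-19), maturation, regression to the mean and reporting bias may contribute in either direction.
2. Describe the comparison with the South African arms as descriptive only, and name the differences in setting, program version and tools.
3. Define the RQ5 analysis set as every dyad enrolled in Furaha Teens, shown by a baseline survey or register entry, whatever their attendance. Align Table 3 with that definition.
4. Report how many enrolled dyads lack post data, as part of the data flow already promised, and analyse them with the FIML or multiple imputation already planned.

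The cost is wording in the RQ5 text and Table 3, plus one count from routine records. No new data are collected. RQ5 can then claim less about impact, and results for all enrolled dyads will lean more visibly on missing-data assumptions.
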